#### Analysis of the primary endpoint

Each patient’s allocation to the different analysis populations (full analysis set according to the ITT principle, PP analysis set, safety analysis set) will be defined prior to the analysis. The allocation will be documented in the statistical analysis plan prior to database closure. During the data review, deviations from the protocol will be classified as minor or major. Major deviations from the protocol will lead to the exclusion of a patient from the PP analysis set.

The primary analysis will be performed using a Cox proportional hazards regression (*α* = 5%, two-sided) with covariates treatment group, age, duration of T2DM, and a stratification for each center. Confirmatory analysis will be based on the ITT population, with ICA-r imputation for missing values [33].

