**Methods:**

The DiaSurg 2 trial is a multicenter, open randomized controlled trial comparing RYGB including standardized medical treatment if needed to exclusive standardized medical treatment of T2DM (control group). The primary endpoint is a composite time-to-event endpoint (cardiovascular death, myocardial infarction, coronary bypass, percutaneous coronary intervention, non-fatal stroke, amputation, surgery for peripheral atherosclerotic artery disease), with a follow-up period of 8 years. Insulin-dependent T2DM patients aged between 30 and 65 years will be included and randomly assigned to one of the two groups. The experimental group will receive RYGB and, if needed, standardized medical care, whereas the control group will receive exclusive standardized medical care, both according to the national treatment guidelines for T2DM. Statistical analysis is based on Cox proportional hazards regression for the intention-to-treat population. Assuming a loss to follow-up rate of 20%, 200 patients will be randomly allocated to the comparison groups. A total sample size of *n* = 400 is sufficient to ensure 80% power in a two-tailed significance test at alpha = 5%.

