### Interventions

#### Experimental group

A laparoscopic RYGB will be performed no later than 2 months after allocation to the experimental group. As part of the standardized preoperative assessment, a gastroscopy, laboratory tests, ultrasound of the abdomen, cardiological and endocrinological assessment will be performed.

The operation technique is as follows: The patient is positioned in the supine position 30° (reverse Trendelenburg) after a regular fasting time of 12 h. A single-shot of antibiotic prophylaxis is given (according to local standards of participating centers). Then a 15 mmHg pneumoperitoneum through the left upper abdomen is created. Next, five trocars are placed in the upper abdomen. The liver retractor is then positioned in the right upper abdomen. Initially, the gastroesophageal junction is identified. Then the stomach is transsected by the use of linear staplers to build a pouch of 4–6 cm height and 14–16 mm width. The omentum majus can be transected depending on the individual anatomy. At 70 cm from the ligament of Treitz, an end-to-side gastroenterostomy is performed using either a linear or circular stapler. To reconstruct the passage, a side-to-side jejuno-jejunostomy 150 cm from the gastrojejunostomy is performed (Figure 1). The proximal anastomosis is then checked for leaks by methylene blue.

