#### Secondary analyses

A standard sensitivity analysis will be performed using the PP analysis set. A further secondary analysis will be based on a prioritized set of time-to-event variables, ranging from death from any cause (highest priority), stroke, myocardial infarction, amputation, coronary artery bypass grafting, percutaneous coronary intervention, to peripheral atherosclerotic artery disease (lowest priority). Potential treatment benefit will be assessed by the so-called proportion in favor of treatment [34], which is a multivariate permutation test based on pair-wise comparisons of patients. The outcome of Patient X will be said to be better than Patient Y if a decision can be made based on pair-wise comparisons of the components of the prioritized outcome in decreasing order. Surgical treatment with standardized medical treatment will be said to be better than exclusive standardized medical treatment if the aggregate proportion in favor of treatment is above 97.5 percentile of the proportions obtained via simulation under the assumption of the null hypothesis (that is, by permutation of the group membership of the patients).

All secondary variables will be analyzed descriptively by tabulation of the measures of the empirical distributions (means, standard deviations, quartiles). For binary outcomes, relative frequencies will be reported. Descriptive *P* values of the corresponding group comparisons and associated 95% confidence intervals will be given.

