### Ethical considerations

The surgical procedure examined in this trial is well established and in current daily use. T2DM is associated with high long-term morbidity and mortality [31]. In obese patients, bariatric surgery showed a remission of T2DM in 42% to 78% of patients [17-19]. In obese patients, mortality of RYGB was about 0.16% to 0.5%, and although the operative risk in obese patients is described, mortality and morbidity rates are expected to be lower in non-severely obese patients [20,28]. Respectively, the operative risk is ethically justifiable considering long-term morbidity and mortality. By comparing conventional medical care to surgical treatment point-by-point, differences in the development of T2DM-associated symptoms are possible. Each individual patient in the intervention group justifiably has the potential to end further insulin treatment for T2DM and thus possibly avoid T2DM-associated co-morbidities. Each patient in the control group will receive standardized medical treatment according to the latest S3 guidelines and thus have no handicap by participating in the study. Participants in the control group will be treated by use of the latest S3 Guidelines set forth by the German Diabetes Association [9]. If the study confirms evidence in improving diabetic symptoms in the experimental group and consequently health-insurance funds refund costs for surgical treatment of T2DM, patients randomized within the medical treatment group will be able to switch to the surgery group. Postoperatively, patients will be examined every year for possible side-effects of the surgery, including an assessment of their vitamin and nutritional status.

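### Per-protocol set drops whole patients for deviations arising after randomization, which can bias the sensitivity analysis in either direction, toward RYGB if controls operated on before an event are removed

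*Protocol article*

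**What the plan says.** The Protocol article, Analysis of the primary endpoint, sets out the grading of deviations: "During the data review, deviations from the protocol will be classified as minor or major". It then fixes the consequence: "Major deviations from the protocol will lead to the exclusion of a patient from the PP analysis set". The unit removed is the patient. The text sets no time limit, does not provide for censoring at the deviation, and does not list which deviations are major. Allocation to the analysis sets is to be documented in the SAP before database closure.

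The same section gives the PP set a supporting role: "Confirmatory analysis will be based on the ITT population". Under Secondary analyses: "A standard sensitivity analysis will be performed using the PP analysis set". The Sample size paragraph of Statistical methods nevertheless claims sufficient power for the PP analysis as well as for ITT.

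Two other places bear on which deviations could arise. Experimental group: "A laparoscopic RYGB will be performed no later than 2 months after allocation to the experimental group". Ethical considerations, on controls: "patients randomized within the medical treatment group will be able to switch to the surgery group". That offer depends on a condition, "If the study confirms evidence in improving diabetic symptoms in the experimental group", and on insurers then refunding the cost. No date is attached.

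**The concern.** The primary endpoint is time from randomization to the first composite event. A patient should be counted at risk at time *t* on the basis of what is known by *t*. Whole-patient exclusion for something that happens in year 4 breaks this: the patient disappears from the risk sets of years 0 to 4 because of a later occurrence.

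A control who is operated on in year 4 without a prior event was event-free for four years by construction. Deleting that patient removes event-free control time and no control event from those years, so the control hazard rises artificially. The two arms need not balance. RYGB is a single procedure due within 2 months, so failure to receive it shows up early, whereas a control could be operated on at any point in 8 to 10 years.

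There is a smaller effect at the start. A patient allocated to RYGB whose early infarction or stroke prevents surgery could be removed together with that event, while a control with the same event stays.

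At stake is how the sensitivity analysis is read. Crossover ordinarily dilutes an ITT estimate, so a PP estimate stronger than ITT could be taken for the undiluted effect when part of it is produced by the exclusion rule.

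**Working it through.** **Inputs from the Sample size paragraph of Statistical methods:** 8-year event rates of 20% (control) and 10% (RYGB), exponential event times, 2-year accrual, minimum follow-up 8 years, two-sided 5%, 80% power, 200 per arm. **Assumed, because the document gives no figure:** the fraction *f* of event-free controls who switch, and the switching time *t0*.

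**1. The plan's own figures.**
- Hazards: control −ln(0.8)/8 = 0.0279 per year; RYGB −ln(0.9)/8 = 0.0132 per year. HR = ln(0.9)/ln(0.8) = 0.472.
- Events (Schoenfeld): 4 × (1.960 + 0.842)² / (ln 0.472)² = 55.75, so 56.
- Mean event probability with uniform accrual: (0.2219 + 0.1117)/2 = 0.1668. Patients: 56/0.1668 = 335.7, so 336.

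The stated 0.472, 56 and 336 reproduce, so the model below is on the plan's own footing.

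**2. Deleting controls who switch at *t0* before an event, no treatment effect.** Both arms have hazard λ = 0.0279 and S(t) = exp(−λt). Removing a fraction *f* of those event-free at *t0* from time 0 leaves the control events before *t0* unchanged but shrinks the risk set, so for t < t0 the apparent control hazard is

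λ × S(t) / [S(t) − f·S(t0)].

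Example, f = 20% and t0 = 4: S(4) = 0.894, so 0.20 × 0.894 × 200 = about 36 controls are deleted. The apparent control hazard is inflated by 1/(1 − 0.179) = 1.22 at time 0, rising to 1/(1 − 0.20) = 1.25 just before year 4. After year 4 there is no inflation. Solving the Cox score equation over the whole follow-up averages these:

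| *f* | PP HR, *t0* = 4 | PP HR, *t0* = 5 |
|---|---|---|
| 5% | 0.977 | 0.972 |
| 10% | 0.953 | 0.943 |
| 20% | 0.900 | 0.881 |
| 30% | 0.841 | 0.814 |

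The true HR is 1.00 throughout. Under the planned effect, f = 20% at year 4 moves the HR from 0.472 to 0.426.

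**3. Simulation, no effect, 200 per arm, 2000 runs per scenario, switching unrelated to risk.** The last column is the frequency of a significant result favoring RYGB (nominal 2.5%).

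| Switching by year 8 | PP HR | False significance for RYGB |
|---|---|---|
| 5 / 10 / 20 / 30%, constant rate | 0.97 / 0.95 / 0.89 / 0.82 | 3.7 / 4.3 / 8.1 / 14.9% |
| 10 / 20 / 30%, all after year 4 | 0.92 / 0.83 / 0.74 | 5.9 / 13.6 / 28.5% |

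Censoring at the switch instead of deleting gave HR 1.00 and 2.1 to 2.9% in these scenarios.

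**4. What changes the direction or size.**
- Controls operated on after a non-fatal primary event are deleted too: HR 0.99 to 1.00 at 10 to 30% switching.
- Higher-risk controls switch more often (gamma frailty, variance 0.5): HR 0.97 / 0.95 / 0.92 at 10 / 20 / 30%. Plain censoring then gives 1.02 / 1.06 / 1.09.
- Deletions in both arms at year 4: equal fractions give HR 1.00; 10% of controls with 20% of RYGB patients gives 1.06, against RYGB.

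**5. Events before planned surgery.** 200 × 0.0279 × 2/12 = 0.93, so at most about one deleted event in the RYGB arm.

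**The case against.** A reader might infer that the plan will delete every control operated on during follow-up, and that the PP analysis therefore favors RYGB even with no effect. The document supports neither step.

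- **Classification.** Nowhere is surgery in a control named as a major deviation. The grading is left to the data review and the allocation to the SAP, which is normal practice.
- **Occurrence.** The switch described under Ethical considerations depends on the study confirming evidence and on reimbursement. It carries no date and may well fall after the analyzed follow-up. A switch that the protocol permits need not count as a deviation at all. It does not establish crossover at year 4 or at any other time in follow-up.
- **Direction.** The rule applies to both arms, and late deviations deleted from the RYGB arm push the other way.
- **Size.** The switching rates are assumed. At 2% switching at year 4 the HR is 0.991. Under no effect about 400 × 0.2219 = 89 events are expected, so the standard error of log HR is about 2/√89 = 0.21, and a shift to 0.95 to 0.98 is small beside it. A move from 0.47 to 0.43 under the planned effect would change no conclusion.
- **Role.** ITT is confirmatory, and removing whole patients is the conventional PP definition.

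All of this stands, and it limits how large the problem is and which way it points. It does not remove the problem. The choice of major deviations is deferred, but the consequence is stated here: the patient is excluded, whenever the deviation arose. No list of major deviations in the SAP cures that for those arising after randomization, unless the SAP also replaces the consequence.

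**Conclusion.** The point holds in conditional form. The stated rule makes membership of the PP set depend on events after randomization, so the PP hazard ratio can be biased by an amount and in a direction that cannot be known in advance. If surgery in a control before a primary event is graded major, and those operated on after an event are kept, the bias is toward RYGB: negligible to small at 5% switching or less, and material at 20 to 30% (HR 0.90 to 0.84 for switching at year 4). These figures rest on the plan's exponential model, on switching unrelated to risk, and on assumed switching rates. Early deletions in the RYGB arm add at most about one event.

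Only the PP sensitivity analysis is affected. The matter is still worth correcting, because that analysis is the named check on the ITT result and the protocol claims power for it.

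**What to change.** Amend the PP definition as follows.

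1. Reserve whole-patient exclusion for eligibility violations already present at randomization.
2. For a major deviation arising after randomization, keep the patient and censor at the date of the deviation, by the same rule in both arms.
3. Keep every primary event that precedes the deviation, including events between randomization and planned surgery.
4. Because this censoring may be informative, add a supporting analysis with inverse-probability-of-censoring weights built from data already collected: age, diabetes duration, and the yearly HbA1c and insulin dose.

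The cost is a change of wording and some extra analysis work; sample size, visits and the confirmatory analysis do not change. The weighted analysis gives slightly wider intervals and depends on a correct model for the deviation with no important unmeasured predictors, which is why it is proposed as supporting.

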#### Secondary analyses

A standard sensitivity analysis will be performed using the PP analysis set. A further secondary analysis will be based on a prioritized set of time-to-event variables, ranging from death from any cause (highest priority), stroke, myocardial infarction, amputation, coronary artery bypass grafting, percutaneous coronary intervention, to peripheral atherosclerotic artery disease (lowest priority). Potential treatment benefit will be assessed by the so-called proportion in favor of treatment [34], which is a multivariate permutation test based on pair-wise comparisons of patients. The outcome of Patient X will be said to be better than Patient Y if a decision can be made based on pair-wise comparisons of the components of the prioritized outcome in decreasing order. Surgical treatment with standardized medical treatment will be said to be better than exclusive standardized medical treatment if the aggregate proportion in favor of treatment is above 97.5 percentile of the proportions obtained via simulation under the assumption of the null hypothesis (that is, by permutation of the group membership of the patients).

All secondary variables will be analyzed descriptively by tabulation of the measures of the empirical distributions (means, standard deviations, quartiles). For binary outcomes, relative frequencies will be reported. Descriptive *P* values of the corresponding group comparisons and associated 95% confidence intervals will be given.

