### Randomization

Randomization will be performed after assessment of the inclusion and exclusion criteria and informed consent of the patient to participate in the study. Randomization will be performed at a ratio of 1:1 for the two treatment groups, using an online randomization tool (http://www.randomizer.at) which enables block randomization and stratification for each center. Four hundred patients will be recruited according to the sample size calculation in order to prevent random error and achieve sufficient strength for hypothesis testing of the primary endpoint.

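### The proportion-in-favour test permutes treatment labels without regard to centre, although allocation is blocked and stratified by centre; if centres differ in risk, the test is valid but conservative

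*Protocol article*

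**What the plan says.** Four statements in the protocol article bear on this.

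- **Randomization.** "Randomization will be performed at a ratio of 1:1 for the two treatment groups", using an online tool "which enables block randomization and stratification for each center".
- **Analysis of the primary endpoint.** The Cox model is stratified by centre. "Confirmatory analysis will be based on the ITT population".
- **Secondary analyses, status of the test.** "A further secondary analysis will be based on a prioritized set of time-to-event variables", ordered from death from any cause down to peripheral arterial disease and compared pair by pair.
- **Secondary analyses, decision rule.** "Surgical treatment with standardized medical treatment will be said to be better than exclusive standardized medical treatment" if the aggregate proportion "is above 97.5 percentile of the proportions obtained via simulation under the assumption of the null hypothesis". The article then explains how that null is simulated: "that is, by permutation of the group membership of the patients".

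The last clause does not say whether labels move across the whole trial, within centre or within block. The next paragraph adds: "All secondary variables will be analyzed descriptively by tabulation".

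**The concern.** A permutation test takes its justification from re-drawing allocations as the trial drew them. Here the design balances the arms within each centre, so differences in risk between centres cannot favour either arm by more than a partly filled block. Free shuffling of all labels does let them: many shuffled allocations put too many patients from a high-risk centre into one arm. The simulated proportions then spread more widely than the proportion the trial could produce by chance, and the 97.5th percentile lies too far out.

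What is at stake is power. The design rests on 56 events, and a prioritized comparison that gives up power to centre differences wastes information that the trial already holds. The primary analysis takes centre into account; this analysis, as worded, does not.

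**Working it through.** **The plan's own figures.** The only figure given for this test is its threshold: the 97.5th percentile is a one-sided 2.5% test, equal to one side of the two-sided 5% primary test. No sample size or power is stated for it. The primary design figures reproduce:

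- HR = ln(0.90)/ln(0.80) = 0.472.
- Schoenfeld events = 4 × (1.960 + 0.842)² / (ln 0.472)² = 55.8, so 56.
- With exponential times, 2-year accrual and 8-year minimum follow-up, the event probabilities are 0.2219 and 0.1117, mean 0.1668. Then 56/0.1668 gives 336 patients.

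**Mechanism.** Give each patient a score: wins minus losses against all other patients. The statistic is the sum of scores in the surgical arm. Under free permutation its variance is proportional to the total variance of the scores. Under within-centre permutation it is proportional to the within-centre variance only. Let r² = total variance / within-centre variance. With 1:1 allocation in every centre both references have the same mean, so the true one-sided size of the free version is about 1 − Φ(1.96 r). Since r is about 1 without centre effects and larger with them, the error goes in the safe direction.

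**Seven-level null simulation.** From the article: N = 400, 1:1, the seven priority levels, 8 to 10 years of follow-up, threshold 2.5% one-sided. Assumed: 10 or 20 equal centres, blocks of 4, component risks of 2-8% at 8 years, independent components, normally distributed centre log-hazards, no loss to follow-up. There were 999 permutations per trial. Both permutation schemes were applied to the same simulated trials.

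| Centres | Centre SD | Trials | Free | Within block |
|---|---|---|---|---|
| 10 | 0 | 1500 | 3.1% | 3.3% |
| 10 | 0 | 3000 | 2.3% | 2.0% |
| 10 | 0.5 | 1500 | 2.1% | 2.7% |
| 10 | 0.5 | 3000 | 2.5% | 2.7% |
| 20 | 0.5 | 1500 | 2.0% | 2.5% |
| 10 | 1.0 | 1500 | 1.1% | 2.3% |
| 10 | 1.0 | 3000 | 1.4% | 2.9% |
| 20 | 1.0 | 1500 | 1.3% | 2.9% |

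The Monte Carlo standard error is √(0.025 × 0.975/1500) = 0.4 points, or 0.3 points with 3000 trials. With no centre effect the two schemes do not differ in a consistent direction. At SD 0.5 the free version is lower in all three runs, though each gap is small. At SD 1.0 the gap is clear.

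**Back-check.** A size of 2.0% corresponds to 1.96 r = 2.054, so r² = 1.10. Sizes of 1.4% and 1.1% correspond to 2.197 and 2.290, so r² = 1.26 and 1.37. On this reading between-centre differences make up about 1 − 1/1.10 = 9% of the score variance in the first case and 20-27% in the others.

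**Power.** A simpler simulation used two levels (death, then cardiovascular event), 20 centres of 20 patients, HR 0.472 and 2000 replicates:

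- SD 0.5: 49.9% free against 52.2% within centre, a loss of 2.3 points.
- SD 0.8: 45.3% against 51.3%, a loss of 6.0 points.

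These figures show the order of the loss. They are not the power of the planned seven-level test.

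**The case against.** **The article never says that labels are shuffled over the whole trial.** That is true. The clause may only explain what the null hypothesis means, and restriction to strata can be set in the statistical analysis plan, which the article says will exist. What stands is that the clause is worded as a definition, and that centre is named for randomization and for the Cox model but not here. A programmer who follows the text would permute freely. If the analysis plan already restricts the permutation, only the sentence needs correcting.

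**The effect is small and rests on assumptions.** This also stands. At SD 0.5 the size is barely distinguishable from nominal, and no sample size depends on this test.

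**Two stronger readings are tempting, and the document supports neither.**

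- A reader might infer that the mismatch produces false positives. The simulations show none; the test errs on the cautious side.
- A reader might infer that the rule for calling surgery better, which sets no condition on the primary result, opens a second route to a superiority claim. In the seven-level simulation either test favoured surgery in 2.7-4.1% of null trials (the two-level version gave 3.8-4.6%; two independent tests would give 1 − 0.975² = 4.9%). In 0.5-1.4% the prioritized test did so without a primary win. These rates matter only if the test is treated as co-primary. The article reserves the confirmatory role for the primary Cox analysis, files this test under secondary analyses, and treats secondary variables descriptively. What remains is a tension in wording between a pass/fail rule and descriptive status.

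**Conclusion.** The point holds as a modest one about efficiency. Read literally, the permutation does not mirror the allocation, and the test is valid but conservative when centres differ in risk. One-sided size is about 2.0-2.5% at a centre log-hazard SD of 0.5 and 1.1-1.4% at SD 1.0, against 2.5% nominal. Within-block permutation gave 2.0-3.3% across all scenarios, which is consistent with nominal given the simulation error. The cost is a few points of power at SD 0.5 to 0.8, and nothing if centres do not differ; power at SD 1.0 was not computed.

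This rests on the assumed number of centres, block size, component risks and heterogeneity, none of which the article gives, and on reading the randomization section to mean that the tool's blocking and centre stratification are used. The direction of the effect follows from the design; its size depends on the assumptions. The confirmatory analysis is untouched.

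**What to change.** State in Secondary analyses that group membership is permuted within centre, and within block where block membership is known. Leave the pairwise comparisons and the proportion in favour of treatment unchanged: forming pairs only within centre, or weighting by centre, would change what is estimated and is not needed to correct this.

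Add a sentence that the rule for calling surgery better is supportive of the confirmatory Cox analysis and not an alternative to it.

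The cost is two sentences and a small change to the permutation code. Centre is already needed for the primary model, so no new data are required. The one practical limit is that labels in a centre with patients in only one arm cannot move; those patients still count in the statistic. The change should be made before outcome data by group are seen.
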